**Figure 1 F1:**
[figure not shown]
Flow chart of the study.

In addition to the nutritional counseling, the couples in the intervention group have the opportunity to take part in a group meeting discussing nutritional issues. Couples willing to participate receive a free taxi-card to arrive to and from the meeting.

### Outcome

A primary outcome measure is change in AD patients’ weights. Secondary outcomes are changes in their energy, protein, and other nutrient intakes retrieved from food diaries, AD patients’ functional ability [20,24], cognitive functioning (MMSE) [19], neuropsychiatric symptoms (NPI, Cornell) [21-23], and caregiver burden (Zarit burden scale) [17]. In addition, HRQOL [16] and use of health services will be assessed during the on year follow-up.

### Statistical analyses

Sample size is calculated based on AD patient’s expected weight change, with a standard deviation of 3.6 kg [6], and type I error of 5%, 80% power. For an expected weight difference between intervention and control patients of 2 kg, 50 patients are needed in each group to show statistical difference. Data will be analyzed on an intention to treat basis. Imputation methods of “the last observation carried forward” (LOCF) and worst rank score will be used.

Data are analyzed using a SPSS statistical program. Intervention and control groups will be compared at baseline; categorical variables will be tested by a Chi-squared test (X^2^) or Fischer’s exact test, and continuous variables by two-sided t-test or Mann–Whitney U-test as appropriate.

Qualitative data will be collected by interviewing subjects during the nutritionist’s visits. The case studies will be transcribed and content analyses carried out. The aim of the analyses will be to analyze difficulties and positive factors in the daily lives of the families that may explain differences in success of nutritional care between subjects.

All data will be securely stored at The Society for Memory Disorders Expertise in Finland. Computerized data will be available only to the members of the research team. The analyzed data will be cleared of all the recognition information, and only ID numbers will be used.

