## Background

Older individuals with Alzheimer disease (AD) living at home with their spouses are an important target group for nutritional care [1] because weight loss and malnutrition are common problem among them [2-4]. Weight loss is a predictive factor of mortality, and it decreases AD patients' and caregivers' quality of life (QOL) [5,6]. Furthermore AD patients often suffer from frailty, sarcopenia, functional impairments, and comorbidities [7]. Their old spousal caregivers often also have comorbidities and functional disabilities [8]. The possibilities of nutritional care in this patient group remain largely unexplored [9].

Nutritional interventions may have beneficial effects on nutritional status and nutrient intake of AD patients [6,10-13]. Several controlled studies have suggested that nutritional supplements increase body weight of AD patients at risk of malnutrition. In an intervention study, weight gain of AD patients was achieved when nutritional supplements were taken for three months [14]. Similarly, Lauque et al. [10] showed that AD patients’ body weight significantly increased with oral nutritional supplements given for three months. A nutrition educational program directed at AD patients and their spouses had a positive effect on AD patients’ weights and their cognitive function [6,13].

However, further studies on the benefits of nutritional care and ways of implementing it are needed [15]. Nutritional care and tailored nutritional counselling are important and largely unexplored means of maintaining the health and QOL of AD patients and their caregivers.

Although nutritional care has been examined and proven effective in randomized, controlled settings in a few multinational studies [1,6,13], the effects of nutritional care on functional ability, health, QOL and use of health services among the aged have not been investigated.

The aim of this study is to investigate whether tailored individualized nutritional counselling and care have an effect on the weight, nutrition, functioning, and QOL of AD patients and their spouses.

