### Randomization

The couples are randomized into clusters of six. The randomization is performed as follows: investigators write down identification numbers of each couple on six pieces of papers, which are then folded so that the numbers cannot be seen. A person unrelated to the investigation then chooses three pieces of paper and the couples with these ID numbers are signed to the intervention group.

All participating couples are assessed at baseline and at the end of the trial with methods described previously. In addition, all AD patients’ and their spouses’ weights are measured at six months.

The nutritionist visits and weighs the intervention couples in their homes also at 3 and 9 months. Nutritional counseling and care are tailored according to each intervention couples needs and consists of 4–8 home visits by the nutritionist Table 1.

**Table 1 T1:** Study assessments and timetable

**Assessment**	**Baseline assessments**	**Telephone interview**	**3-month visit**	**6-month visit**	**9-month visit**	**12-month assessment**

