**Spouse**						
Background information^1^	x					x
Nutrition anamnesis	x					x
3-day food diaries^1^	x	x				x
Zarit^1^	x					x
MNA	x					x
MMSE	x					x
15 D HRQOL^1^	x					
IADL	x					x
Weight, BMI	x		x^2^	x	x^2^	x
Grip strength	x					x
Use of health services				x		x

^1^filled at home.

^2^only in intervention group.

*AD *Alzheimer’s disease, *CDR *degree of dementia [20], *MMSE *Mini mental state examination [17], *MNA *Mini Nutritional Assessment [16], *BMI *body mass index, *NPI *Neuropsychiatric inventory [21,22], *Cornell *depression test [23], *IADL *Instrumental activities of daily living [24], *15 D *HRQOF [18], *Zarit *Zarit burden scale [19].

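### LOCF and worst rank score are planned without saying which governs the primary weight change, and LOCF biases that comparison when weight is falling

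*Protocol article*

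**What the plan says.** The Outcome section sets the primary endpoint: "A primary outcome measure is change in AD" patients' weights. I read this as the change to 12 months, the end of the intervention.

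The Statistical analyses section sizes the trial on a mean difference of 2 kg with SD 3.6 kg and "type I error of 5%, 80% power". It then states: "Data will be analyzed on an intention to treat basis". The imputation sentence follows, naming LOCF and worst rank score: "LOCF) and worst rank score will be used". It links neither rule to an outcome, to a reason for missingness or to a primary result.

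All patients are weighed at baseline, 6 and 12 months. The Randomization section adds: "The nutritionist visits and weighs the intervention couples in their homes also at 3 and 9 months". Footnote 2 of Table 1 marks these extra weights "only in intervention group".

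On the expected course, the Background says of people with AD that "weight loss and malnutrition are common problem among them". The Abstract likewise describes deteriorating nutritional status, and the Discussion calls the study population old and frail.

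**The concern.** LOCF assumes that weight stops changing when a patient leaves. In a population expected to lose weight, the loss after dropout is not counted. If the arms decline at different rates, a true difference is diluted. If they decline at the same rate but lose different proportions of patients, a difference appears that does not exist.

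Worst rank score does something else. It places a patient below everyone observed and gives an analysis of ranks, so it does not estimate the mean difference in kg on which the trial is sized. Because the text does not assign the two rules, a reader cannot tell which produces the primary result or how deaths enter it.

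**Working it through.** **1. The plan's own figure.** With a two-sided test (stated only for the baseline comparisons, "continuous variables by two-sided t-test", and assumed here for the sample size), n per group = 2 × (1.960 + 0.842)² × 3.6² / 2² = 2 × 7.85 × 12.96 / 4 = 50.9, so 51. The stated 50 gives 79.3% power. The sample size is reproduced and is not in question. With 102 AD patients there are about 51 per arm.

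**2. Assumptions.** The documents give no dropout rate and no weight trajectory. I assume linear mean change, dropout spread evenly over 12 months, and dropout unrelated to weight. Under the last assumption an analysis of completers is unbiased, so any shift below comes from LOCF alone.

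**3. Average time of the carried weight.**
- Intervention (weighed at 0, 3, 6, 9): (0 + 3 + 6 + 9) / 4 = 4.5 months. This supposes that the home weights enter LOCF, which the text does not say.
- Control (weighed at 0, 6): (0 + 6) / 2 = 3.0 months.

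**4. Mean change under LOCF.** For dropout proportion d, true 12-month change Δ and mean carried time m: (1 − d)Δ + dΔm/12.

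True difference 2 kg, intervention 0 and control −2 kg:

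| Dropout per arm | Control mean under LOCF | Difference |
|---|---|---|
| 10% | 0.9(−2) + 0.1(−0.5) = −1.85 | 1.85 kg |
| 20% | 0.8(−2) + 0.2(−0.5) = −1.70 | 1.70 kg |
| 30% | 0.7(−2) + 0.3(−0.5) = −1.55 | 1.55 kg |

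Other trajectories with the same 2 kg difference give similar results at 20%: 1.75 kg for +2 versus 0, and 1.68 kg for −1 versus −3.

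**5. No true effect, both arms losing 2 kg.**
- Intervention, 10% dropout: 0.9(−2) + 0.1(−0.75) = −1.875.
- Control, 25% dropout: 0.75(−2) + 0.25(−0.5) = −1.625.
- False difference: 0.25 kg in favour of control, the arm with more dropout.
- With the dropout proportions reversed: −1.6875 versus −1.85, or 0.16 kg in favour of the intervention.

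For the 0.25 kg case, SE = 3.6 × √(2/51) = 0.713. The shift is 0.25/0.713 = 0.35 SE, and the two-sided rejection rate is Φ(−1.61) + Φ(−2.31) = 0.064. Simulation, which also lets LOCF reduce the variance, gives about 6.8%.

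**6. The schedule difference alone.** With equal dropout and equal decline, the shift is d × annual loss × (4.5 − 3.0)/12. For 20% and 2 kg this is 0.05 kg; for 30% and 3 kg it is 0.11 kg.

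**7. Power.** With a true 2 kg difference, simulation gives LOCF about 76-77% at 10% dropout and 73% at 20%. By formula, completers alone give 76% (about 46 per arm) and 71% (about 41 per arm). LOCF costs no power against that comparator.

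**8. Secondary outcomes.** In Table 1, MMSE, CDR, NPI, Cornell, IADL, Zarit, MNA and grip strength have no measurement between baseline and 12 months. If LOCF is applied to them, the carried value is always the baseline, so every dropout scores a change of exactly zero. This follows from the schedule and needs no dropout assumption.

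**The case against.** The strongest reply is that a condensed article need not assign each rule to each outcome and reason for missingness. LOCF for withdrawals with worst rank for deaths would fit the sentence and would be coherent. This stands against one tempting inference: that both rules are meant for the same missing weights, leaving the sponsor to choose once the results are known. Simulation shows what would turn on such a choice. With a true 2 kg difference and 20% dropout per arm, power is about 73% under LOCF with a t-test and 40% if every dropout takes the worst rank in a Mann-Whitney test. But the documents do not say that the rules overlap, so that charge is not made.

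Two other stronger readings also fail. Dividing the shrunken effects of 1.85 and 1.70 kg by an unchanged SE of 0.713 would suggest power of 74% and 67%. LOCF also shrinks the variance, so those figures are too low, and the fall from 80% reflects dropout itself. A reader might also see the unequal weighing as a main cause of bias, but alone it contributes only about 0.1 kg.

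It is fair, too, that the bias is modest, depends on assumed dropout, and is conservative in step 4. The reply does not rescue LOCF itself. The article names it as a method to be used, so it is not a detail left to another document. A mixed model has a weakness of its own: it implicitly gives deceased patients a 12-month weight, so the repair needs a rule for deaths.

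**Conclusion.** The point holds in limited form. The plan commits to LOCF in a disease where it expects weight to fall, and leaves open which rule governs the primary weight change, which reason for missingness each covers, and which result decides.

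Under the stated assumptions, a true 2 kg difference becomes about 1.7 kg at 20% dropout per arm. With no effect and 10% versus 25% dropout, a false difference of about 0.25 kg arises, with type I error of about 6-7% instead of 5%. These are illustrations: size and direction depend on dropout and trajectories that the documents do not give. If mean weight did not change in either arm, dropout of this kind would cause no such bias.

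For the scales measured only at baseline and 12 months, the effect is certain if LOCF is applied to them. Worst rank may be intended for deaths, but the text does not say so, and it cannot supply the difference in kg.

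**What to change.** Replace the imputation sentence with the following.

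- **Primary analysis:** a mixed model for repeated measures on AD patients' weight at 6 and 12 months, the follow-up times common to both arms, with baseline weight, arm, time and arm-by-time, and no single imputation. The estimate is the 12-month difference in kg. The intervention-only 3- and 9-month weights stay out of this comparison.
- **Deaths:** state explicitly how they are handled, and keep worst rank as a named sensitivity analysis for them.
- **Other sensitivity analyses:** add a delta-adjusted analysis. Drop LOCF, or label it a sensitivity analysis.
- **Outcomes measured only at 0 and 12 months:** baseline-adjusted ANCOVA instead of LOCF.

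The cost is wording and slightly more analysis work. No new data or patients are needed, follow-up was still under way according to the Trial status section, and SPSS, the stated software, fits mixed models. The downside is a missing-at-random assumption, which the sensitivity analyses probe.

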## Discussion

This intervention trial investigates the effect of individualized, home-based tailored nutritional care on home-dwelling AD patients and their aged spouses. A nutritionist visits the intervention couples in their homes 4–8 times according to their nutritional needs. In addition, the intervention group is given oral and written counseling on exercise and how to perform daily exercise routine to strengthen muscles. If the intervention couple is unable to complement their diet naturally and clear deficiencies in protein and/or other nutrients are observed, the couple will be given complementary daily drinks that contain energy, protein, and other nutrients. Dietary supplements are recommended to AD patient and spouse when necessary. In addition, intervention couples are advised to take a 20 μg vitamin D supplement daily year round. The control group is given a written guide on nutrition of the older people.

Our study has several strengths. All AD patients have an established diagnosis of AD; they were recruited from the Finnish drug registry. As AD is a risk factor for deterioration of nutritional status, this intervention enables this problem to be dealt with at early stage of the disease. Old spouses also often have multiple diseases and disabilities, and thus, are an important target group for nutritional care. Tailored nutritional care may enable the aged couple to live in their home longer. Findings of this trial are directly applicable to real life, allowing nutritionists and healthcare professionals to focus on nutritional interventions for the older people. Tailored nutritional intervention that addresses the nutritional needs of AD patients and their caregivers is described in detail.

The study also has potential drawbacks. First, our study population is old and frail with many comorbidities, thus, being vulnerable to various complications. Second, a sufficient difference may be difficult to obtain between intervention and control groups. Contamination of the control group is probably not a problem because home-based nutritional interventions are not available in Finland to AD patients and their spouses.

To our knowledge, this study is the first of its kind conducted in Finland; nutritional interventions in a home-based setting before for AD patients and their spouses have not been performed. Our study provides new and detailed information on intervention methods that can be implemented to decrease malnutrition and its adverse effects in frail old individuals. This gives caregivers and healthcare personnel information on nutritional treatment possibilities. Optimally, nutritional rehabilitation will support older persons’ nutrition, maintain or increase functional ability, reduce the use of health services, and improve QOL.

## Trial status

Trial is still ongoing. Patient recruitment has been completed and follow-up is being conducted.

## Abbreviations

AD: Alzheimer disease; BMI: Body Mass Index; CDR: Clinical Dementia Rating Scale; HRQOL: Health-related quality of life; IADL: Instrumental activities of daily living; MMSE: Minimental State Examination; MNA: Mini Nutritional assessment; NPI: Neuropsychiatric Inventory.
